## Abstract

**Background**: Familial pulmonary fibrosis (FPF) can be defined as pulmonary fibrosis in two or more first-degree family members. The first-degree family members of FPF patients are at high risk of developing FPF and are eligible for screening. Reproducible studies investigating risk factors for disease are much needed. **Methods**: Description of the screening study protocol for a single-center, prospective cohort study; the study will include 200 asymptomatic, first-degree family members of patients with FPF who will undergo three study visits in two years. The primary objective is determining the diagnostic value of parameters for detection of early FPF; the secondary objectives are determining the optimal timing of the screening interval and gaining insight into the natural history of early FPF. The presence of interstitial lung disease (ILD) changes on high-resolution computed tomography of the chest is indicative of preclinical ILD; the changes are determined at baseline. The comparison between the group with and without ILD changes is made for clinical parameters (pulmonary function, presence of digital clubbing, presence of Velcro-like crackles, blood count, liver- and kidney-function testing, patient-reported cough and dyspnea score) and exploratory parameters. **Discussion**: This study will be the first large-size, prospective, longitudinal cohort study for yearly screening of asymptomatic family members of FPF patients investigating the diagnostic value of parameters, including lung function, to detect early FPF. More effective screening strategies could advance early disease detection.

## 1. Introduction

Within the group of interstitial lung diseases (ILD), pulmonary fibrosis (PF) is a chronic, often progressive process associated with high mortality. Studies show that 5–25% of patients with PF have familial disease [1,2,3,4]. Although definitions vary between studies, here we define familial pulmonary fibrosis (FPF) as PF being present in two or more first-degree family members. FPF most commonly presents as idiopathic pulmonary fibrosis (IPF) [2,3,4], but other ILDs such as rheumatoid arthritis (RA)-ILD, hypersensitivity pneumonitis (HP)-ILD and unclassifiable ILD are also observed [1,2].

FPF is usually inherited in an autosomal-dominant way. In that case, first-degree relatives of FPF patients have a 50% chance of also carrying the disease-causing mutation and are therefore at high risk of developing FPF [3,4,5]. Disease course, including decline in forced vital capacity (FVC) [6] and mortality [2,4,7,8] in FPF patients, is comparable with sporadic IPF. While there is no specific treatment for adult FPF patients, retrospective analyses suggest that antifibrotic treatment has similar safety and effectivity as in patients with IPF or progressive PF [9,10,11]. In studies of patients with FPF, diffusing capacity for carbon monoxide (DLCO) and FVC are often already impaired at diagnosis, with values around 50% and 70% of normal, respectively [6,12,13]. Timely diagnosis is thus important to fully benefit from therapeutic intervention.

Current guidelines of the Dutch Association of Clinical Genetics recommend actively informing first-degree relatives of patients with genetic diseases about their increased risk for disease and the possibilities of genetic screening [14]. The St Antonius ILD Center of Excellence and the Universitair Medisch Centrum (UMC) Utrecht Clinical Genetics Department have put in place a clinical protocol to screen for early pulmonary disease in asymptomatic, high-risk relatives older than 18 years of age. Current clinical screening involves a high-resolution computed tomography (HRCT) of the chest with a five-year interval and an annual medical examination consisting of anamnesis, pulmonary function test, blood tests, and physical examination. This screening protocol was based on parameters that are used for the detection of PF in symptomatic persons, as well as information gathered from studies investigating patients with FPF or asymptomatic family members [6,15,16,17]. However, evidence on the diagnostic value of these markers, notably in early disease, is scarce and the intervals were chosen arbitrarily.

The value of an HRCT scan as a screening tool in asymptomatic, at-risk relatives is evident. Several studies have investigated the prevalence of ILD changes on HRCT scans in asymptomatic relatives of familial or sporadic PF patients. They reported surprisingly congruent percentages of 14–23% of relatives with ILD changes [15,17,18,19,20]. However, data for other potentially interesting screening parameters, including pulmonary function, are limited. As yearly radiographic imaging in healthy subjects is not advised due to radiation exposure and costs, other screening parameters to reliably detect disease development and progression are needed. Additionally, little is known about the early course of disease in FPF, and data from screening and follow-up programs will be most informative.

In this article, we describe the design of the FLORIS study (optimizing screening detection for early disease detection in FamiLial pulmOnaRy fibrosIS) which will include 200 first-degree family members of patients with FPF and is currently in progress. The presence of ILD changes on the baseline HRCT scan will be used as the indicator for presence of early pulmonary disease, and we will assess the predictive value and follow-up dynamics of lung function, physical examination, blood markers, and questionnaires. In addition, the aim is to provide insight into the natural history of early familial disease as this is currently largely unknown.

## 2. Materials and Methods

### 2.1. Objectives and Endpoints

The primary objective of the FLORIS study is to determine the diagnostic value of parameters for early disease detection in first-degree relatives of patients with FPF. To this end, the presence or absence of ILD changes on a baseline HRCT scan (see Figure 1) will be used to determine the predictive value for early disease of a set of clinical and exploratory parameters (see Table 1).

As secondary objectives, the study aims to gain insight into the natural history of FPF and to determine the necessary interval between screening visits. Secondary endpoints will assess the change in parameters between baseline and follow-up after one and two years within each group separately, and analyze differences between the groups with and without ILD-changes (see Figure 1).

### 2.2. Design and Participants

The FLORIS study is a prospective, single-center study performed at the ILD Center of Excellence at the St Antonius Hospital in Nieuwegein, The Netherlands. Two hundred first-degree family members of patients with FPF will be screened according to a predefined screening protocol, with a two-year follow-up. Participants must be first-degree relatives of patients with FPF, asymptomatic, and at least 18 years old. Exclusion criteria are a previous diagnosis of ILD or pregnancy at baseline. If a participant becomes pregnant during the follow-up, they will not be excluded. Potential participants will receive study information via clinical geneticists of the UMC Utrecht, through the national ILD section of the Dutch Society of Pulmonologists, and through other sources such as the PF patient foundation. Current patients with FPF will also be given a letter with information about the study which they can hand to their family members. If patients are willing to participate, written informed consent will be obtained, and patients will be screened for eligibility.

### 2.3. Hospital Visits

Hospital visits will take place at baseline, after 1 year (±1.5 months) and after 2 years (±1.5 months). Study procedures include the standard of care procedures as present in the current clinical screening protocol. Additionally, several exploratory parameters are investigated (see Table 1). At baseline, patient characteristics including age, sex, smoking status, family health history and ILD-related history will be collected and an HRCT scan will be performed to assess the presence of ILD changes. During each visit, participants will be examined by a physician. Pulmonary-function tests will also be performed, blood samples will be collected and patients will fill out digital questionnaires. Study measurements are described in Table 1. Any health event occurring to the participants during the study will be noted upon each study visit.

### 2.4. Assessment of Preclinical ILD

At baseline, subjects will be stratified into two groups based on the presence (ILD changes group) or absence (no ILD changes group) of ILD changes on HRCT scan (Figure 1). ILD changes are defined as extensive disease, familial interstitial lung abnormalities (FILA) or minimal FILA (see Box 1). The definition of FILA is based on the position paper of the Fleischner Society on interstitial lung abnormalities (ILA) [21]. The position paper does not consider abnormalities identified during screening for ILD in high-risk groups, including familial ILD, as ILAs because they are not incidental. The Society suggests the term preclinical ILD for such cases, however, this suggests that subjects have ILD which is not always the case. Therefore, we added familial (F) to refer to the context of the findings, which together makes FILA. To define all possible abnormalities during screening, minimal FILA will be defined as FILA in less than 5% of the lung zone (see Box 1).

A thoracic radiologist will assess the HRCT scan. All the findings of study visits will be discussed with an expert pulmonologist in the field and, when necessary, in a multidisciplinary discussion. If ILD changes or other abnormalities in clinical parameters are found that warrant evaluation, participants will remain in the study, but will also be referred to regular care for examination by a general practitioner or pulmonologist.

Box 1Definition of ILD changes in the FLORIS study.ILD changes on HRCT scan in first-degree family members of FPF patients are defined as:
Extensive disease: non-trivial abnormalities present in three or more lung zones (a)FILA: Any of the following non-dependent abnormalities involving >5% of a lung zone: traction bronchiectasis, honeycombing, ground-glass or reticular abnormal-ities, lung distortion and non-emphysematous cysts (a)Minimal FILA: Any of the following non-dependent abnormalities involving <5% of a lung zone: traction bronchiectasis, honeycombing, ground-glass or reticular abnormalities, lung distortion and non-emphysematous cysts
(a) Concepts are based on the definition of ILA by Hatabu et al. [21] for incidental findings and adjusted to a screening setting of high-risk relatives

### 2.5. Parameters

#### Physical Examination

At each study visit, a physician will inspect the presence of digital clubbing and perform lung auscultation. Bilateral clubbing is a common phenomenon in ILD (e.g., IPF, HP, sarcoidosis) [22]. In familial IPF, finger clubbing was seen in 13–30% of the patients at diagnosis [6,7].

Studying auscultation, Moran-Mendoza et al. observed that fine crackles were present in 93% of IPF patients upon initial presentation [23]. Similar findings are found in familial IPF patients, with studies reporting Velcro-like crackles at diagnosis in 93–96% of the patients [6,7]. The presence of Velcro-like crackles may hence be a valuable tool in early diagnosis. A recent review on early diagnosis of fibrotic ILD mentioned the training of primary care physicians for better identification of Velcro-like crackles and electronic auscultation tools, as possible aids in the process of auscultation during the diagnostic progress [24]. In RA patients, analysis for Velcro-like crackles by an algorithm of recordings of an electronic stethoscope showed a high diagnostic accuracy for ILD, with a sensitivity of 93.2% and a specificity of 76.9% when compared to HRCT scan [25].

In the FLORIS study, participants will undergo digital auscultation in addition to the standard analogue method with a non-validated, electronic stethoscope (eKuore One Wireless, Valencia, Spain). This otherwise regular stethoscope is connected to a device that records lung sounds, which can then be transferred through Bluetooth to a smartphone application. This allows the sound recordings to be linked to the exact position of the lung. Afterwards, computer analysis will be performed for the detection of Velcro-like crackles.

### 2.6. Lung Function Testing

Lung function tests consist of spirometry, single-breath diffusion and body box. Key variables are FVC, DLCO (corrected for hemoglobin) and total lung capacity (TLC). DLCO is measured by the standard diffusion test, i.e., the carbon-monoxide diffusing lung capacity single-breath technique. TLC is measured in the body box. In relatives of patients with PF, those with ILA showed relative reductions in FVC, TLC and DLCO [16].

### 2.7. Blood Markers

Blood samples will be taken at every visit to measure the standard of care, complete blood count and liver and kidney function tests. This is of particular interest as mutations in telomere-related genes cause a significant proportion of FPF. Hematological abnormalities are rather common in patients with telomere-related disease, with red blood cell macrocytosis in 24–41%, thrombocytopenia in 8–54% and anemia in 17–27% of patients [12,13,26,27]. In individuals with telomere-related gene mutations, liver disease is also seen, and liver enzymes can be elevated [28,29]. In screening of at-risk subjects, liver disease was reported in around 2.7–5% of subjects [15,17]. Kidney disease has also been linked to short telomere syndrome [30]. In the exploratory segment of the study, the levels of the blood biomarkers Krebs von den lungen 6 (KL6), surfactant protein-D (SP-D), Chemokine (C-C motif) ligand 18 (CCL18) and matrix metalloproteinase 7 (MMP7) will be analyzed. Elevated levels of KL-6, SP-D and MMP7 were associated with a diagnosis of PF according to a meta-analysis [31]. Interestingly, Kropski et al. found that increased levels of MMP7 and SP-D were significant predictors of HRCT scan abnormalities in asymptomatic family members of patients with familial disease when compared with healthy control subjects [17]. Moreover, elevated levels of KL6 [32], CCL18 [33] and SP-D [34,35] have been associated with lung function decline or poor survival in IPF. Biomarker analysis will be performed according to the standard protocol in our laboratory [36,37]. Samples may be used to explore other putative blood biomarkers in addition to the aforementioned known biomarkers.

### 2.8. Questionnaires

Subjects will receive digital questionnaires prior to each visit (see Table 1). Hunninghake et al. did not observe a significant difference in the frequency of reported respiratory symptoms between relatives with or without ILA screened for PF [16]. On the other hand, a retrospective study by Hewson et al. showed that IPF patients were significantly more likely to present with symptoms of dyspnea and cough, and to a lesser extent fatigue, in the five years prior to diagnosis [38]. Patient-reported parameters on respiratory symptoms may thus be potentially informative for early disease detection.

The Medical Research Council (MRC) dyspnea scale was assessed longitudinally in chronic ILD. A MRC dyspnea score at baseline (in IPF) or an increase in score over time (in IPF and non-IPF ILD) has been associated with clinical progression of the disease [39]. Cough is a major symptom in IPF [40], and an independent predictor of disease progression in IPF [41]. Self-reported cough severity can be measured through a visual analogue scale (VAS) [42]. It is composed of a 100 mm scale with the extremes at ‘no cough’ and ‘worst possible cough severity’, whereby the subjects mark their cough severity.

In order to better understand the natural history of PF, two additional questionnaires on fatigue and health status will be administered to investigate whether symptoms not directly related to the lung may be present. The Fatigue Assessment Scale (FAS), a 10-item general fatigue questionnaire, will be used to measure fatigue. To measure health status, the EuroQOL-5 Dimensions (EQ-5D) will be used. This tool consists of two parts: a 5-dimension list (mobility, self-care, usual activities, pain/discomfort and anxiety/depression) with a 5-level classification (ranging from no problems to extreme problems), and the EQ-VAS. Both the FAS [43] and the EQ-5D [44,45,46] have been used in ILD before.

Other questionnaires at baseline will include ‘demographics and expositions’ and ‘diseases in the family’, which are already standard procedure at the ILD outpatient clinic; there will be a short follow-up questionnaire at visits 2 and 3. A non-validated questionnaire with questions regarding risk perception, reasons for participating and prior screening will also be included at baseline.

### 2.9. MUC5B rs35705950 Genotyping

The minor allele of the *MUC5B* promoter variant rs35705950 is an important risk factor for IPF and FPF, with a minor allele frequency of over 33% in white patients in contrast to 9% in healthy controls [47]. Recent studies showed that this *MUC5B* risk allele is also associated with other forms of PF [48,49,50,51,52]. Amongst asymptomatic relatives, signs of preclinical PF on HRCT scan were significantly, although only in relatives aged over 60 years [19] or borderline significantly [15] more common in carriers of the *MUC5B* risk allele. Genotyping will be performed according to the protocol described in Van Der Vis et al. 2016 [50].

### 2.10. Six-Minute Walk Test

The six-minute walk test (6MWT) is used in patients with chronic respiratory disease, with the test being primarily a test of physical capacity [53,54]. Walking distance, heart rate and O2 saturation (sat), together with subject length, weight, Borg Dyspnea and Leg Fatigue scales (1–10), will be noted according to standard protocol. Previous studies showed a shorter six-minute walk distance is present in patients with an increased risk of mortality for patients with IPF, chronic obstructive pulmonary disease, ILD, pulmonary hypertension and those awaiting transplantation [53,55]. Interestingly, among a group of IPF patients with relatively mild disease (defined as FVC% predicted ≥ 80%), oxygen desaturation during the 6-MWT was the only significant predictor of death or progression within 12 months [56]. Little is known about the value of the 6MWT in earlier stages of the disease. However, the 6MWT is a validated test that can be easily performed outside of the hospital and requires few resources, making it a potential cost-effective screening tool.

### 2.11. Study Registration

The study was approved by the Medical Ethics Committee United (MEC-U, NL75303.100.20) and registered at https://clinicaltrials.gov/ct2/show/NCT05367349 (accessed on 20 December 2022); ID NCT 05367349.

### 2.12. Sample Size

The sample size was calculated based on our own retrospective data and literature. In pilot screening, we detected ILD changes in 13 of 73 (18%) asymptomatic, at-risk relatives, while in the literature, ILD changes were seen in 16–23% of the HRCT-scans [15,18,19,57]. In the present study, we will include 200 participants, with an expected ratio of 37 participants with the presence of ILD changes and 163 participants with the absence of ILD changes at HRCT scan.

### 2.13. Statistical Analysis

Categorical variables, including presence/absence of Velcro-like crackles, presence/absence of clubbing, MRC dyspnea scale, and *MUC5B* rs35705950 genotype will be expressed as numbers with percentages. Continuous variables, including FVC, TLC, DLCO (corrected for hemoglobin), VAS Cough score, MMP7 level, CCL18 level, KL-6 level, SP-D level, and 6MWT (distance in meters, sat O2 rest, sat O2 after 6MWT, sat O2 nadir, and sat O2 rest minus sat O2 nadir) will be displayed as means with standard deviations or medians with standard error, where appropriate.

The primary objective will be tested using a chi-square test or Fisher-exact test (as appropriate for categorical variables) and Student’s *t*-test or Mann–Whitney U test for continuous variables. Univariate logistic regression will be used to test which parameters differ between the groups. Parameters that are found to be diagnostic in univariate analysis with *p* < 0.20, will subsequently be assessed in a multivariate logistic regression analysis using the backward method to determine which are the strongest predictors for ILD changes on HRCT scan at baseline. In case too many parameters meet the *p* < 0.20 criterion, a cut-off of *p* < 0.10 will be used.

The secondary objective will be tested using the paired *t*-test, or Wilcoxon signed-rank test for the differences between the groups, and a repeated measure ANOVA test for the differences within the same group over time. After year 2, linear mixed models will be used to determine the strength of change of the parameters over time within and between both groups.

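### The ordered MRC dyspnea scale is compared between groups with tests that ignore its order

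*Protocol article*

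**What the plan says.** Section 2.13 (Statistical Analysis) sorts the parameters into two types. The first list reads "Categorical variables, including presence/absence of Velcro-like crackles, presence/absence of clubbing, MRC dyspnea scale" and goes on to the MUC5B genotype; these are shown as numbers with percentages. For the comparison of participants with and without ILD changes, categorical variables get a "chi-square test or Fisher-exact test (as appropriate for categorical variables"). The rank test is offered for the other type only: "Mann–Whitney U test for continuous variables".

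The same section then adds a second univariate step: "Univariate logistic regression will be used to test which parameters differ between the groups". The entry rule for the backward model follows: "Parameters that are found to be diagnostic in univariate analysis with *p* < 0.20". The article does not say whether MRC enters that regression as a score or as a factor.

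Section 2.8 (Questionnaires) reads the scale as ordered. For MRC it reports that "an increase in score over time (in IPF and non-IPF ILD) has been associated with clinical progression of the disease".

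Section 2.12 (Sample Size) plans 200 participants, "with an expected ratio of 37 participants with the presence of ILD changes and 163 participants with the absence of ILD changes". It gives no power, significance level or effect size.

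**The concern.** The clinical question about MRC is whether higher grades go with ILD changes. A chi-square or Fisher test on the full table asks something broader: whether the grade distributions differ in any way. With two groups and k grades, chi-square spreads its sensitivity over k − 1 degrees of freedom (2 for three grades, 4 for five). A trend test or Mann–Whitney U puts it all on the one direction of interest. If the real difference is a shift upwards, the stated tests are the less sensitive choice.

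A missed signal would have a consequence. The Discussion says that parameters without predictive value may be dropped from the clinical screening protocol, and it hypothesises that patient-reported symptoms help to predict early disease. The Abstract lists the dyspnea score among the clinical parameters.

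**Working it through.** **Inputs from the article.** MRC classed as categorical, with chi-square or Fisher-exact as its test (Section 2.13). MRC read as a score that can increase (Section 2.8). Participants asymptomatic (Section 2.2). Expected groups of 37 and 163 (Section 2.12).

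**The stated split.** The pilot rate is 13/73 = 17.8%. 200 × 13/73 = 35.6, and 200 × 0.18 = 36, against 37 stated (37/200 = 18.5%). The literature range of 16–23% gives 32 to 46. The stated split is reasonable and is used below. The article states no power, so there is none to reproduce.

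**Assumptions not in the article.** Four MRC distributions for the group without ILD changes; a proportional-odds shift with odds ratio (OR) 2, 2.5 or 3; a two-sided 0.05 level.

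**Shift.** For each cut k, let o = P(Y > k)/(1 − P(Y > k)) without ILD changes. With ILD changes, P(Y > k) = OR·o/(1 + OR·o). Example, 90/8/2% at OR 2.5: o = 0.10/0.90 = 0.111; 2.5 × 0.111 = 0.278; 0.278/1.278 = 0.217. So 78.3% remain in the lowest grade, and the full distribution is 78.3/16.9/4.9%.

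**Power at 0.05 (%), 20,000 simulated studies per setting.** The Mann–Whitney test is corrected for ties.

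| Grades without ILD changes (%) | OR | Chi-square | Trend | Mann–Whitney |
|---|---|---|---|---|
| 90/8/2 | 2 | 28.7 | 29.6 | 31.0 |
| 90/8/2 | 2.5 | 45.4 | 47.6 | 49.8 |
| 90/8/2 | 3 | 61.3 | 63.8 | 66.5 |
| 80/15/4/1 | 2 | 36.4 | 40.1 | 42.2 |
| 80/15/4/1 | 2.5 | 57.1 | 62.5 | 66.3 |
| 80/15/4/1 | 3 | 74.0 | 78.5 | 81.9 |
| 70/20/7/2/1 | 2 | 40.1 | 46.0 | 49.6 |
| 70/20/7/2/1 | 2.5 | 61.4 | 68.7 | 73.2 |
| 70/20/7/2/1 | 3 | 78.0 | 84.8 | 88.0 |
| 60/25/10/4/1 | 2 | 41.3 | 51.1 | 53.1 |
| 60/25/10/4/1 | 2.5 | 64.3 | 74.9 | 77.2 |
| 60/25/10/4/1 | 3 | 80.0 | 88.4 | 90.0 |

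The smallest gain over chi-square is 29.6 − 28.7 = 0.9 points (90/8/2, OR 2, trend). The largest is 77.2 − 64.3 = 12.9 points (60/25/10/4/1, OR 2.5, Mann–Whitney). Within 90/8/2 the range is 0.9 to 66.5 − 61.3 = 5.2 points. At OR 1 all three tests rejected in about 5% of studies (4.5 to 5.5%), so the gain is not bought with extra false positives.

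**Fisher-exact.** Every simulated table had an expected count below 5. For example, with 80/15/4/1% at OR 2.5 the top grade holds 163 × 0.01 + 37 × 0.025 = 2.6 participants in all, of whom 2.6 × 37/200 = 0.5 are expected in the smaller group. Fisher is therefore the likelier choice. At OR 2.5 and 0.05 (4,000 studies per setting):

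- 80/15/4/1%: Fisher 59.7%, chi-square 57.1%, trend 62.5%, Mann–Whitney 66.3%.
- 70/20/7/2/1%: Fisher 65.3%, chi-square 61.4%, trend 68.7%, Mann–Whitney 73.2%.

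Fisher stays 66.3 − 59.7 = 6.6 and 73.2 − 65.3 = 7.9 points below Mann–Whitney, and about 3 points below the trend test in both cases.

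**The p < 0.20 step, only if MRC is entered as a factor.** A factor in univariate logistic regression behaves much like the chi-square test, and a single score much like the trend test. At the 0.20 level and OR 2.5, chi-square v trend is 68.3 v 69.5, 79.4 v 82.3, 82.2 v 86.6 and 84.7 v 90.5 in the four distributions. Over OR 2 to 3 the gap runs from 0.9 to 6.9 points.

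**The case against.** The best defence is that the article commits to less than a critic may read into it. Several points stand.

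- A reader might infer that MRC will enter the logistic regression as several dummy terms and so be more likely to fail the p < 0.20 filter. The article does not say this. The filter follows directly on the logistic step. If MRC enters there as one score, order is used and the filter loses nothing. Coding is also something a condensed article may leave to a fuller document. The classification as categorical points towards a factor, but does not settle it.
- A reader might blame the small number of cases. The loss comes from ignoring order, and 37 is an expected count. A small group only makes lost power harder to spare.
- A reader might extend the point to the MUC5B genotype. Section 2.13 does not fix its number of categories, Section 2.9 speaks of carriers, and no calculation here covers it.
- The distributions and odds ratios are assumed. Asymptomatic relatives may cluster in the lowest grade, where little is gained. Section 2.8 also cites a study of relatives that found no significant difference in respiratory symptoms with or without interstitial lung abnormalities.
- Simulating proportional odds favours an order-using test by construction. Against a non-monotone pattern it can lose.

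These points limit the size and reach of the concern. They do not remove its core, because the type of variable and the test for that type are both written in Section 2.13.

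**Conclusion.** The point holds for the between-group comparison. The plan classes an ordered scale as categorical and gives it tests that ignore order, while its own rationale reads the scale as ordered. Under a monotone shift with odds ratio 2 to 3 and groups of 37 and 163, an order-using test gains roughly 1 to 13 points of power at 0.05 over chi-square, and about 1 to 5 points if some 90% are in the lowest grade. Fisher-exact narrows the gap somewhat but does not close it. All sizes rest on assumed grade distributions.

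An effect on entry to the multivariable model is conditional on MRC being entered as an unordered factor, and is not established. The planned tests keep their error rate. This is a minor efficiency matter for one parameter among many.

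**What to change.** Add one sentence to Section 2.13: the MRC dyspnea scale is compared between groups with the Mann–Whitney U test (already in the plan) or a trend test, and enters the logistic regression as one ordinal term, with sparse top grades merged by a rule set before the grades are looked at by HRCT group. Keep counts and percentages for display.

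The change needs no new data and no more participants. Its one statistical cost is less power against a non-monotone pattern, which the displayed counts would still let a reader see.

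### Relatives are recruited through families with no limit of one per family, but the named primary tests assume independent participants, so p-values may be too small if several relatives per family enrol

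*Protocol article*

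**What the plan says.** Section 2.2 of the protocol article defines the sample: "Two hundred first-degree family members of patients with FPF will be screened according to a predefined screening protocol". Potential participants hear of the study through clinical geneticists, the national ILD section of the pulmonologists' society, the patient foundation and, in addition, affected patients: "Current patients with FPF will also be given a letter with information about the study which they can hand to their family members". The eligibility criteria in that section do not restrict enrolment to one relative per family.

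Section 2.12 expects "an expected ratio of 37 participants with the presence of ILD changes and 163 participants with the absence of ILD changes".

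Section 2.13 fixes the primary analysis: "The primary objective will be tested using a chi-square test or Fisher-exact test (as appropriate for categorical variables", with Student's t or Mann–Whitney for continuous parameters. Univariate logistic regression follows. Parameters with p<0.20 (or p<0.10 if too many qualify) go into a backward multivariable logistic model. Paired tests and repeated-measures ANOVA serve the secondary objective. Linear mixed models are added after year 2 for change over time within and between the two groups. No family term, GEE or robust variance is mentioned.

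On inheritance, the Introduction says: "FPF is usually inherited in an autosomal-dominant way", and that in such cases "first-degree relatives of FPF patients have a 50% chance of also carrying the disease-causing mutation".

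**The concern.** Handing letters to relatives is a natural way to enrol siblings, or a parent's several children, from one family. Such participants may resemble each other in ILD risk, because families differ in causal gene, *MUC5B* status, age range and shared exposures. They may also resemble each other in the parameters under test: *MUC5B* genotype is inherited, and section 2.7 motivates the blood tests by telomere-gene mutations, which run in families. When outcome and parameter both cluster, a test that counts each relative as a separate observation understates the standard error.

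Here p-values decide which parameters enter the multivariable model, with only about 37 participants with ILD changes expected. The Discussion intends the results to help choose who needs an HRCT scan and which parameters may leave the screening protocol. A marker that looks stronger than it is could therefore affect practice.

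**Working it through.** **The plan's own figure.** The pilot rate is 13/73 = 17.8%, and 200 × 13/73 = 35.6. The stated 37 of 200 is 18.5%. The literature range of 16–23% gives 32 to 46. The 37/163 split is therefore reproduced closely enough, and 18.5% is used as the prevalence below.

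**Assumed inputs.** The article gives neither the number of relatives per family (m) nor any intraclass correlation (ICC). I take m = 2 to 4 and a marker ICC of 0.3 to 0.5. For ILD status I take several scenarios:

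- *Pure Mendelian transmission in every family.* Each participant is already a first-degree relative of a patient. Given that the family carries a mutation, each relative inherits it separately with probability 0.5, so carrier status is uncorrelated among them. ICC = 0.
- *Moderate family heterogeneity.* Half the families have 27% risk and half 10%, mean 18.5%. Between-family variance is 0.085² = 0.00723; total variance is 0.185 × 0.815 = 0.1508; ICC = 0.00723/0.1508 = 0.048.
- *Liability correlation 0.5.* At 18.5% prevalence this is a binary ICC of 0.29.
- *Liability correlation 0.8 (extreme).* Binary ICC of 0.55.

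**Formula.** For a marker unrelated to ILD status, the variance of the group comparison is inflated by DE = 1 + (m − 1) × ICC(marker) × ICC(ILD). The true error of a nominal two-sided test with critical value z is 2 × [1 − Φ(z/√DE)], with z = 1.960 for 5% and 1.282 for the 20% screen.

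| m | ICC marker | ICC ILD | DE | nominal 5% | p<0.20 screen |
|---|---|---|---|---|---|
| 1 | any | any | 1 | 0.050 | 0.200 |
| 4 | 0.5 | 0 | 1 | 0.050 | 0.200 |
| 2 | 0.5 | 0.048 | 1.02 | 0.053 | 0.205 |
| 4 | 0.5 | 0.048 | 1.07 | 0.058 | 0.216 |
| 2 | 0.3 | 0.29 | 1 + 0.3 × 0.29 = 1.09 | 0.060 | 0.219 |
| 2 | 0.5 | 0.29 | 1 + 0.5 × 0.29 = 1.145 | 0.067 | 0.231 |
| 3 | 0.5 | 0.29 | 1 + 2 × 0.5 × 0.29 = 1.29 | 0.084 | 0.259 |
| 4 | 0.5 | 0.29 | 1 + 3 × 0.5 × 0.29 = 1.435 | 0.102 | 0.285 |
| 4 | 0.5 | 0.55 | 1 + 3 × 0.5 × 0.55 = 1.83 | 0.147 | 0.343 |

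**Simulation check.** The t-test was simulated with a null marker, 200 relatives and 18.5% prevalence, marker ICC 0.5:

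- Mendelian transmission only: about 0.05 for m = 2, 3 and 4.
- Moderate heterogeneity: 0.05 to 0.06.
- Liability correlation 0.5: 0.065 for m = 2 and 0.106 for m = 4, with the screen at 0.227 and 0.291.
- Liability correlation 0.8, m = 4: about 0.15, with the screen at 0.34 to 0.36.
- One relative per family, or a marker that does not cluster: about 0.05.

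The formula and the simulation agree.

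**Precision.** With independent data, 37 against 163 detects (1.960 + 0.842) × √(1/37 + 1/163) = 0.51 SD with 80% power at two-sided 5% (both levels assumed; the article states neither). At DE = 1.435 this becomes 0.51 × √1.435 = 0.61 SD.

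**The case against.** The strongest reply concerns the mechanism. A reader might infer from the Introduction's account of autosomal-dominant inheritance that ILD changes must cluster among relatives. That does not follow in this sample. Every participant is selected as a relative of an affected patient, so the contrast between carrier and non-carrier families is largely removed, and transmission within families is independent. The check confirms that this alone produces no inflation. Clustering has to come from differences between these already enriched families, and the article does not quantify them. This part of the reply stands.

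It is also fair that the number of relatives per family is unknown. Patients may pass on a letter, but other recruitment routes exist. With pairs and modest correlations the effect is negligible, and a p<0.20 filter that acts as 0.22 does little harm.

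A third reply is that variance estimators and random-effects structures are commonly left to a full protocol or SAP. This stands for the linear mixed models, whose random effects are simply not given, so it would be too broad to say that every planned analysis ignores family. It does not dispose of the primary analysis. The article names chi-square, Fisher, t and Mann–Whitney tests, which in standard form cannot carry a family effect, and a reader following section 2.13 as written would run them on related participants. Logistic regression could be given a family-robust variance within the present wording, but nothing says that it will be.

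**Conclusion.** The concern holds in conditional form. The named primary tests do not match a sample recruited through families without a limit of one relative per family. If several relatives per family enrol, and families differ in both ILD risk and the marker, p-values may be too small, most of all for inherited or family-shared markers. Under the assumed ranges, the true error of a nominal 5% test lies between about 5% (moderate heterogeneity) and about 10% (liability correlation 0.5, four relatives per family). The screen lies between about 0.20 and 0.29.

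A reader might go further and conclude that the p-values are certain to be too small, or that the error will reach 15% or more. The documents do not support either. The larger figure needs four relatives from every family and a liability correlation of 0.8 together, and with one relative per family there is no inflation. Section 2.13 mentions no confidence intervals; those from the named models would be affected in the same way as the p-values, under the same conditions.

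This should be fixed as a cheap improvement. It does not threaten the design.

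**What to change.** - Record a family identifier at enrolment. Family history is already collected at baseline.
- Fit the univariate and multivariable logistic models by GEE with family as cluster, or with cluster-robust variance by family, using a small-sample correction. With an independence working correlation the odds ratios are those of ordinary logistic regression; only the standard errors change.
- Base the p<0.20 (or p<0.10) screening decisions on these p-values, and keep the chi-square, Fisher, t and Mann–Whitney tests as descriptive.
- Add a family random intercept above the participant level in the linear mixed models.
- Report the number of families and the distribution of relatives per family. An analysis with one relative per family is a useful sensitivity check.

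The cost is one linking variable and some analysis wording, with no extra visits or participants. The downside is somewhat wider intervals. If almost every family turns out to contribute one person, the results will barely change.
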